#### Efficacy

##### • Primary variable

The two-sample T-test was used for VAS for bothersomeness of low back pain at baseline and at 8 weeks for the comparison of the two groups and to determine differences from baseline. ANCOVA and two-sample T-test was used between the differences at baseline VAS and 8 week VAS for each groups. Also, a 95% confidence interval was added for all analyses.

Repeated measure two factor analysis will be used to analyze the difference and mean change among baseline, and 4, 6, 8, 12 and 24-week VAS, difference and mean change between groups, and interaction between groups and observed time. If necessary, a mixed model approach was also used.

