### Sample size determination

Generally, a level of significance of α = 0.05 and a power of 1-ß = 0.80 were used. For two arms (control - sham acupuncture, experimental - real acupuncture), we considered the two sample t-test model.

Experimental group: real acupuncture

Control group: sham acupuncture

Primary parameter: VAS for bothersomeness at 2 months after beginning of treatment

Expected mean difference and common standard deviation between two groups: 1.5 on a 0-10 VAS for bothersomeness, SD = 2.73

Drop-out rate: 20%

Sample size determination:(1)

where,

*N *: total sample size

*n*_*t *_: sample size for experimental group

*n*_*c *_: sample size for control group

r: number of experimental group

s: number of control group

λ: ratio of experimental and control sample size (λ = *n*_*t*_/*n*_*c*_)

In the trial, r = 1, s = 1 and λ = 1 were assumed, and then *N *= *n*_*t *_+ *n*_*c *_

To determine optimal sample size, we considered the following hypotheses of interest and formulas of sample size

Under hypotheses *H*_0_: μ_c _= μ_t _*H*_1_: μ_c _≠ μ_t _

sample size:(2)

μ_t _: mean of experimental group

μ_c _: mean of control group

σ^2 ^: common variance between two groups

α: probability of type 1 error (significance level)

ß: probability of type 2 error

Z_α/2_: α/2th quantile of standard normal distribution

Z_ß _: ßth quantile of standard normal distribution(3)

μ_c_-μ_t _= 1.5, σ = 2.73(Reference: Cherkin et al)[25]

Using formulas (1) above:(4)

For the equal allocation for the two groups, total sample size considering drop-out rate of 20% was calculated as 130 subjects.

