### Statistical methods and analysis

All statistical analysis was performed in the principle of ITT analysis (Intention-To-Treat analysis) and PP analysis (Per-Protocol analysis). In the case of ITT analysis, we applied the LOCF (Last Observation Carried Forward Analysis) rule. For all statistical analysis, SPSS Win. Ver.14.0 and a significance level of 0.05 were used.

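### No analysis or population is named as deciding the week-8 primary comparison: three week-8 tests and a repeated-measures analysis stand side by side in ITT and PP, each at 0.05

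*Protocol article*

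**What the plan says.** The section Primary outcome measures sets a single endpoint, the bothersomeness VAS at the 8-week follow-up. Sample size determination states a two-sided hypothesis of equal means at 2 months and plans for a two-sample t-test.

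Under Efficacy, Primary variable, the article then lists:

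- a t-test on the score: "The two-sample T-test was used for VAS for bothersomeness of low back pain at baseline and at 8 weeks";
- a t-test on the change, and ANCOVA: "ANCOVA and two-sample T-test was used between the differences at baseline VAS and 8 week VAS for each groups";
- an analysis over baseline and weeks 4, 6, 8, 12 and 24, covering time, group and their interaction: "Repeated measure two factor analysis will be used to analyze the difference and mean change";
- a mixed model, if needed, with no condition for its use.

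Statistical methods and analysis applies all of this to two populations: "All statistical analysis was performed in the principle of ITT analysis (Intention-To-Treat analysis) and PP analysis (Per-Protocol analysis". The level is the same throughout: "For all statistical analysis, SPSS Win. Ver.14.0 and a significance level of 0.05 were used". The section on baseline homogeneity also lets ANCOVA covariates depend on the outcome of baseline significance tests.

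No section names the deciding analysis or population, sets an order, or states what result counts as success.

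**The concern.** This is not a matter of detail left to an analysis plan. The article itself gives several competing tests of one hypothesis equal standing. The tests use overlapping data but can fall on different sides of 0.05. If they disagree, nothing on the page says which one answers the trial's question, and a reader of the results could not tell whether the reported test was the intended one. The trial sets out to verify an effect on which it calls the earlier evidence contradictory, so the deciding test should not be open.

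**Working it through.** **1. The plan's own figure.** Inputs from Sample size determination: difference 1.5, SD 2.73, two-sided 0.05, power 0.80, 1:1 allocation, 20% drop-out.

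n per arm = 2σ²(z₀.₉₇₅ + z₀.₈₀)²/δ² = 2 × 2.73² × (1.960 + 0.842)²/1.5² = 52.0, so 52. Then 52/(1 − 0.20) = 65 per arm, or 130 in total. This reproduces the stated 130. It covers one two-sample t-test in one population.

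**2. Counting the tests.** Week 8: t-test on score, t-test on change, ANCOVA, which makes 3. Repeated measures: group and group-by-time, which makes 2. In two populations there are 3 × 2 = 6 week-8 tests and 5 × 2 = 10 in all. The optional mixed model and the data-driven choice of covariates are not counted.

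**3. Independence is only an upper limit.** 1 − 0.95^m gives 14.3% for m = 3, 26.5% for m = 6 and 40.1% for m = 10. These tests share the same patients and values, so the figures overstate the error and simulation is needed.

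**4. Null simulation.** 65 per arm, six visits, no treatment effect, 20% random drop-out, LOCF in ITT, completers as PP, baseline VAS as the ANCOVA covariate. Equal correlation r between visits and the baseline SD are assumptions, because the article gives neither. Post-baseline SD is 2.73. There were 8,000 trials per row at baseline SD 2.73 and 4,000 at 1.44. Entries are the percentage of trials with at least one p < 0.05.

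| Baseline SD | r | 3 week-8 tests, ITT | same, ITT + PP | plus repeated measures, ITT | all, ITT + PP |
|---|---|---|---|---|---|
| 2.73 | 0.3 | 9.1 | 12.3 | 15.6 | 21.4 |
| 2.73 | 0.5 | 9.3 | 13.2 | 15.0 | 21.0 |
| 2.73 | 0.7 | 9.9 | 13.6 | 15.1 | 20.3 |
| 1.44 | 0.3 | 7.8 | 10.5 | 14.3 | 19.4 |
| 1.44 | 0.5 | 7.7 | 10.1 | 14.0 | 19.0 |
| 1.44 | 0.7 | 8.0 | 10.8 | 13.7 | 18.6 |

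The value 1.44 is the SD of a uniform spread over 5 to 10, (10 − 5)/√12, chosen because entry requires a VAS of at least 5 at screening. Simulation error is about half a percentage point. Further runs with other drop-out settings and a baseline SD of 1.5 stayed within 7-11% (first column) and about 10-15% (second).

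**5. One test fixed in advance.** The week-8 t-test in ITT alone rejected in 4.7-5.2% of null trials in the 8,000-trial runs, which is the nominal 5%. Naming ANCOVA but letting either ITT or PP count gave 6.2-7.1%, so the population has to be named as well.

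**6. Power of the candidate lead analysis, 52 per arm.** The unadjusted t-test has about 79%. With baseline VAS as a covariate the residual SD is 2.73√(1 − r²): 2.60 at r = 0.3 and 2.36 at r = 0.5. Power is then about 83% and 89%.

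**The case against.** **A reader might infer that the trial's false-positive rate is well above 5%.** The document does not support that as a fact. It nowhere says that any one significant result counts as success. The inflation arises only under such a rule, or if the test is picked after the data are seen. A full protocol or analysis plan may name one test, and the rate is then 5%.

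**There is a partial signal of a lead analysis.** One endpoint and one hypothesis are fixed, the sample size uses a two-sample t-test, and the Primary variable section opens with such a test. This stands as a hint but settles nothing. That section has two t-tests (score and change) beside ANCOVA, each in two populations.

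**The repeated-measures analysis is not a week-8 test.** This is correct. It uses all visits and answers a related question, so the figures with and without it are kept apart.

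Three further criticisms are tempting and should not be made:

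- *The change-score test loses power.* With 52 per arm it has 65%, 72% and 79% at r = 0.3, 0.4 and 0.5, but only if the baseline SD is 2.73. Values confined to 5-10 cannot have an SD much above (10 − 5)/2 = 2.5. At 1.44 the power is 81%, 85% and 89%.
- *An unpaired test is applied to paired data.* The sentence is awkward, but it refers to comparing the two groups. A two-sample t-test on change scores between arms is valid.
- *The treatment effect is diluted.* A constant 1.5 over five post-baseline visits becomes 1.5 × 5/6 = 1.25 in a group main effect that includes baseline. The plan also tests group by time, where the effect is not lost. What remains is a choice of contrast, taken up in the fix.

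**Conclusion.** The point holds as a failure to designate: neither the deciding analysis nor the deciding population is named for the week-8 primary comparison. Its size is conditional. If any result could count, or the choice followed the data, the type I error would be about 7-11% for the three week-8 tests in ITT, about 10-15% with PP, and about 20% with the repeated-measures tests in both sets. One pre-named test gives 5%. The correlations (0.3-0.7), baseline SD (1.4-2.73) and PP share (about 80%) are assumptions. The error exceeded 5% in every scenario run, and the lower ends of the ranges belong to the narrower baseline spread that the entry rule makes more plausible. The sample size calculation is not in question.

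**What to change.** Name one confirmatory analysis: the between-arm difference in week-8 bothersomeness VAS in the ITT population, by ANCOVA with baseline VAS as a covariate fixed in advance, two-sided 0.05, with a 95% confidence interval. Centre may be added as a covariate, since randomisation was done per centre. The baseline covariate should not depend on a baseline significance test.

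Label the unadjusted t-test, the change-score t-test, the PP analysis and the repeated-measures or mixed-model analysis as supportive, with no efficacy claim from them alone. In the repeated-measures analysis, use baseline as a covariate, or base the treatment comparison on the group-by-time contrast rather than on a group main effect that includes baseline.

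The change is to wording only. It needs no new data, the total stays at 130, and under the planning assumptions the adjusted analysis has somewhat more power than the t-test used for planning. The sponsor gives up the choice between analyses.

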##### • Secondary variable and others

For the variable, VAS for pain intensity, Oswestry Disability Index (ODI), SF-36, EQ-5D, repeated measure two factor analysis was used to analyze the difference and mean change among baseline, 4, 6, 8, 12 and 24-week VAS, difference and mean change between groups, and interaction between groups and observed time. If necessary, a mixed model approach was also used.

For medication use, the Chi-square test was used to analyze the different types of drugs between the groups, dose of drug and frequency of dose in a day among baseline, 4, 6, 8, 12 and 24-week VAS. Repeated measure two factor analysis was used to analyze the difference and mean change between groups, interaction between groups and observed time. If necessary, a mixed model approach was also used.

#### Safety

All adverse effects were recorded and described as frequency and percentage. For the comparison of adverse effects between groups, the Chi-square test or Fisher's exact test were performed.

### Data handling

Investigators entered the information required by the protocol into the Case Report Forms (CRFs). Non-obvious errors or omissions were entered into data query forms, which were returned to the investigational site for resolution. The data from all centers were gathered and summarized with respect to demographic baseline characteristics, effectiveness and safety observations.

## Discussion

We adopted the visual analogue scale for bothersomeness (not pain) as the primary outcome measurement. This is because the target disease of this study is chronic low back pain. According to the clinical experience, we observed that some patients with chronic pain tend to be very bothered by even a small amount of pain and others are not bothered by even moderate pain. In clinical practice, we frequently find it is more essential and effective to try to improve bothersomeness due to chronic pain than to try to reduce that pain itself.

Various randomized clinical trials that have investigated the efficacy of acupuncture tend to use different types of control groups, such as sham acupuncture, placebo acupuncture and a waiting list [8,9,26,27]. In this study, we chose placebo acupuncture (non acupuncture points) combined with sham acupuncture device. We believe that it is more valid to combine placebo acupuncture with sham acupuncture as the control group, in order to isolate the specific effects of the technique from the non-specific analgesic ones.

The results of this trial will be available in July 2010
